### Interim analyses {21b}

N/A: No interim analyses are planned.

### Methods for additional analyses (e.g., subgroup analyses) {20b}

N/A: No subgroup analyses are planned.

### Methods in analysis to handle protocol non-adherence and any statistical methods to handle missing data {20c}

Given the small target sample size (*n* ≈ 50) and in case of arbitrary pattern of missing data, if applicable, multiple imputations for incomplete multivariate data will be performed on all missing data, using the *Amelia R* package [69, 70]. Our comprehensive imputation *R* code will be made available.

### Plans to give access to the full protocol, participant-level data, and statistical code {31c}

Any full-protocol-related information or material (e.g., consent form or therapy guide), statistical code, and participant-level dataset will be made available upon request.

## Oversight and monitoring

### Composition of the coordinating center and trial steering committee {5d}

Two investigators will oversee the supervision of the overall research trial in their investigation center. Another co-coordinator investigator will supervise the trial opening and assisting its course (e.g., handbook psychotherapy implementation and adherence) on its early phase. A steering committee, composed of each research investigator, the research scientific committee, the research methodologist and a promoter agent designed the research, wrote the protocol and will be in charge of deciding about the trial update and continuity.

### Composition of the data monitoring committee, its role and reporting structure {21a}

Given our trial design open-label nature, no data monitoring committee will be required to protect blinding of the research psychiatrists and psychologists. Two data managers will be in charge of managing, assessing data entry quality, and providing access to the Research Electronic Data Capture (REDCap) secure web application.

### Adverse event reporting and harms {22}

According to article L1123-10 of the French code of public health, any adverse reaction/incident will be reported through the Ministry of health’s adverse health event reporting portal. Minor adverse events such as fatigue or hypersomnia due to protocol compliance and cocaine abstinence are anticipated. No serious adverse events related to the protocol are anticipated. As soon as the participant consent form is collected and until its participation ending, the trial principal investigator will also inform the promoter and take note of any spontaneous significant participant adverse health event deemed potentially related to the research protocol into the Research Electronic Data Capture (REDCap) secure web application.

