However, VRCET in these studies was either used as an add-on to an active treatment condition, or not compared to a control condition [30], which does not provide further insights into the clinical benefit or risk associated to VRCET over classical CET or CBT. For instance, some evidence suggest that VRCET, and CET more broadly, may increase the risk of relapse among patients treated for nicotine use disorder (NUD), compared to CBT alone [36]. Accordingly, therapeutic interventions for SUD which promote effective coping with lapses are suggested to be the most useful supplement to CET [15]. In line with this, in patients with CUD, positive relationships are shown to exist between beliefs about abstinence self-efficacy, lower urges in high-risk situations and cocaine use up to 3 months post-treatment [37]. Interestingly, memory-focused therapy cognitive therapy (MFCT) is a novel and promising structured CBT around, inter alia, patient’s reliving, cognitive restructure and restructure of sensory images, negative appraisals, and complex emotional responses associated with consolidated cocaine-related memories, as well as the use of general relapse prevention skills [38], and whose the preliminary efficacy in reducing cocaine use and craving was demonstrated in an external RCT on outpatients treated for CUD [39, 40]. Suggested as an adjunctive CBT intervention for CUD [39], MFCT might be of substantial interest for enhancing therapeutic response and preventing risk of relapse of patients involved in our VRCET-based experimental therapeutic arm. Consequently, we decided to combine our VRCET intervention phase with a consecutive MFCT phase, specifically intended to enhance the overall patient’s control over their cocaine craving-related dysfunctional thoughts, emotions, and behaviors up to 3-month post-treatment [39]. Finally, given meta-analytic evidence suggesting that brief therapy formats might enhance the overall effect of CBT for SUD (*N* = 47 studies; [14], both our experimental and control therapeutic arms will be delivered in a brief (3 weeks) and daily (5 days/week) format, which has been shown to be feasible safe and acceptable in outpatients with CUD [39].

Hence, our experimental therapeutic arm will consist of 2 consecutive weeks of daily-delivered VRCET, followed by 1 week of daily-delivered MFCT, whereas the active comparator arm will consist of 3 consecutive weeks of daily-delivered PCET.

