## Assignment of interventions: blinding

### Who will be blinded {17a}

Patients and researchers will not be blinded after assignment to interventions given significant delivery modalities between VR-based and picture-based exposure therapies. Only the data manager in charge of the allocation sequence will be blinded to the assignment.

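### Adverse events enter the trial database through a significance and relatedness filter applied by an unblinded investigator, so harms not measured on schedule cannot be compared fairly between arms

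*Protocol article*

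**What the plan says.** The rule stands in the protocol article under Adverse event reporting and harms {22}. From consent until participation ends, the principal investigator notifies the sponsor and has the task to "take note of any spontaneous significant participant adverse health event deemed potentially related to the research protocol". The place of entry is REDCap, the trial database. The same section names a second channel, under which "any adverse reaction/incident will be reported through the Ministry of health’s adverse health event reporting portal". It also states an expectation: "Minor adverse events such as fatigue or hypersomnia due to protocol compliance and cocaine abstinence are anticipated".

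Under Who will be blinded {17a}, "Patients and researchers will not be blinded after assignment to interventions". Under Confidentiality {27}, the participant code itself includes the assigned arm. Section {21a} provides no data monitoring committee, and its reason concerns blinding alone: "no data monitoring committee will be required to protect blinding of the research psychiatrists and psychologists".

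**The concern.** Two judgements stand between an event and the database: whether it is significant, and whether it is potentially related to the protocol. Both are made by someone who knows whether the participant wore a VR headset and virtually self-administered cocaine or looked at slides on a laptop. An investigator could quite reasonably link distress or dizziness to the headset more readily than to the slides, or could do the reverse out of confidence in the new treatment. Either way, the chance of being recorded may differ by arm.

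The recorded event rate would then mix what happened to participants with how readily it was attributed. A real excess of harm in one arm could be hidden, and a false excess could appear. An event never entered cannot reliably be recovered later. Events expected to be minor, such as fatigue and hypersomnia, would probably fail the significance test in both arms, so tolerability would be under-described even if the filter worked equally.

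**Working it through.** The protocol states no adverse event rate, no safety sample size and no safety power, so there is no figure to reproduce. The check compares passages and then illustrates the size under assumed values.

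**Routes by which a harm can be captured**
- Section {22}, REDCap: significant events deemed potentially related. This is the only database route described for adverse events as such.
- Section {22}, Ministry of health portal: a regulatory channel, not the trial dataset.
- Table 4 and Outcomes {12}: urine strips, Timeline Followback (last 21 days), AWARE and craving at T0, T1, T2 and T3 in both arms. Cocaine use and craving do not depend on section {22}.
- Table 4 and Outcomes {12}: SPIE cybersickness, scheduled during therapy but described for VR exposure; CSQ-8 satisfaction at T1 and T2.
- Section {11b}: reasons for early cessation are documented, and a hospitalization of more than 1 month for something other than CUD is a discontinuation criterion.

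**What is left to section {22}.** High suicidal risk is a non-inclusion criterion at screening, but Table 4 lists no suicidality measure after baseline. An admission shorter than 1 month is not covered by the discontinuation criterion. Such events reach the database only by passing the filter.

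**Size, under assumed values.** For each arm, recorded rate = true rate × probability that an event is recorded. If the true rate p is the same in both arms, the recorded ratio is (p × a) / (p × b) = a / b, whatever p is.

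| Recording probabilities (assumed) | Recorded ratio, true rates equal | Recorded rates if p = 20% |
|---|---|---|
| 80% vs 60% | 0.80 / 0.60 = 1.33 | 16% vs 12% |
| 50% vs 25% | 0.50 / 0.25 = 2.0 | 10% vs 5% |
| 90% vs 30% | 0.90 / 0.30 = 3.0 | 18% vs 6% |

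With 54 randomized 1:1, there are 27 per arm. At p = 20%, 27 × 0.20 = 5.4 events are expected in each arm. Under the second row the database would hold 27 × 0.10 = 2.7 in one arm and 27 × 0.05 = 1.35 in the other.

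**The filter can also hide a difference.** Assume true rates of 20% and 40%, with recording probabilities of 80% and 40% respectively. Recorded rates are 0.20 × 0.80 = 16% and 0.40 × 0.40 = 16%, so a true twofold excess shows as a ratio of 1.

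**If the filter is the same in both arms,** a = b and the ratio is preserved, but both rates are understated by the factor a. The fairness problem therefore rests on the filter differing by arm. The open-label design allows this, but the documents cannot quantify it.

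**The case against.** Several objections have force.

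- **The word only is an inference.** Section {22} does not say that nothing else is entered, and its portal sentence carries no significance filter. This stands as a point of wording. But no other database route for adverse events is described, and the portal does not feed the trial dataset.
- **Spontaneous is ambiguous.** A reader might infer a third filter that admits only volunteered events. The word may equally mean that an event arose by itself. The two firm filters are significance and relatedness.
- **Potentially related is a low threshold.** That is true, and it reduces the loss. It does not make the judgement blind to arm.
- **Attribution might differ by arm for good reason.** If one treatment truly causes more events, more will be judged related. But when only events judged related are kept, a real difference cannot be told apart from a difference in judgement.
- **Other safeguards exist.** Mood is scheduled at each assessment, sessions in both cue-exposure treatments open with listening for difficulties and close with a craving check, and reasons for stopping are recorded. A reader who inferred that early departure or cocaine use goes uncaptured would be wrong. None of these is an adverse event record.
- **The article condenses a fuller protocol.** Forms and event definitions may well sit there. This point concerns a recording rule that the article states, not a detail it omits.

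A reader might also connect this with the background's remark that VRCET and CET "may increase the risk of relapse among patients treated for nicotine use disorder (NUD), compared to CBT alone". That comparison does not carry over: it is with CBT alone in nicotine users, whereas both arms here use cue exposure, and cocaine use is measured on the same schedule in both.

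**Conclusion.** The point holds in a limited form. As written, the plan yields an incomplete harms record, filtered by significance and presumed cause with knowledge of the arm. Adverse events other than cocaine use, craving and cybersickness therefore cannot be compared fairly between arms; suicidality and short admissions are examples. The size is unknown. Under assumed recording probabilities the spurious ratio runs from 1.33 to 3.0, and it would be 1 if the filter worked identically in both arms.

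Two broader conclusions might be inferred and are not supported. The trial can still speak to acceptability, which it defines through CSQ-8 satisfaction and SPIE cybersickness, neither of which passes through section {22}. And the statement that no related serious events are anticipated is an expectation, not a rule that suppresses recording. The conclusion rests on reading section {22} as the sole database route for adverse events.

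**What to change.** Replace the recording rule in section {22}. Enter in REDCap every adverse and serious adverse event in both arms, from consent to T3, whatever the presumed cause. Hold severity and relatedness as separate fields completed after the event is entered, so that neither decides whether it is recorded. Ask one identically worded open question in both arms at T1, T2 and T3. Tabulate all events by arm first and related events second. Reporting through the Ministry portal continues as it is.

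This is a cheap improvement: one additional e-CRF page and a few minutes at visits that already take place, with no change to treatment. The downside is that more unrelated events have to be entered.

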### Frequency and plans for auditing trial conduct {23}

At any stage of the trial, a clinical and independent research associate, designed by the study promoter, will be allowed to audit, and inspect any study member, document, procedure, or data related to the trial conduct in order to guarantee the well respect of participant safety, rights, and data integrity. This inspection can also be solicited from another competent authority, such as the French national agency for the safety of medicines and health products (ANSM). In any case, the investigators will comply with the inquiries from the research sponsor or any other competent authority conducting the audit or the inspection.

### Plans for communicating important protocol amendments to relevant parties (e.g., trial participants, ethical committees) {25}

Any substantial modification brought to the protocol, i.e., at significant risk for participant safety, research result validity, adherence to the planned therapeutic arms, will be addressed under written form to the research sponsor, upon approbation from the French research ethics committee (*Comité de Protection des Personnes – Île-de-France VII*). Other non-substantial modifications will be noticed to the research ethic committee for information purpose. Any modification, including those at risk of plausible incidence on participant benefits or constraints, will be updated to the trial register (i.e., clinicaltrials.gov: NCT05833529).

### Dissemination plans {31a}

Findings of this trial will be disseminated to psychiatry and addictology-related international and national conferences, as well as manuscript publications to peer-reviewed journals. A results summary will be made accessible to study participants and updated to the trial register.

## Discussion

To the best of our knowledge, our project is the first randomized and controlled trial of VRCET for CUD, primarily assessing its efficacy and acceptability as a therapeutic add-on (i.e., combined with MFCT) to reduce both cocaine use frequency and intensity post-intervention (T2) and at 1-month follow-up (T3), as compared with an active control therapy (PCET). Therapeutic evidence on VRCET integrated in broader treatment for SUD are mixed [30]. For instance, a randomized and controlled trial (RCT) in 44 patients hospitalized for alcohol use disorder (AUD) reported a significant decrease of cue-induced self-reported craving and physiological reactivity in an experimental arm combining VRCET with conventional treatment for SUD, compared to conventional treatment [71]. Another RCT in 102 patients with NUD did not observe significant differences in retention and abstinence rates between a CBT + CET experimental arm and a CBT control arm up to 12-month follow-up [36]. Numerous other CET trials in the literature combine habituation-focused interventions with miscellaneous CBT techniques (e.g., coping skills training) into one single exposure session [30]. While authors argue for CET-specific (e.g., increased habituation) and non-specific factors (e.g., reduced substance intake) for explaining cue-induced craving reduction [36, 72], any causal attribution of changes related to VRCET or any other psychotherapeutic condition remain highly limited without a proper comparative design, as intended in our trial [30, 45]. In addition, our CET sessions (VRCET and PCET) will be exclusively habituation-focused, i.e., implying a decrement in cue-induced craving response after its repeated, prolonged, and non-reinforced stimulation [47, 48]. Taken together, our CET comparative design is assumed to bear high internal validity which is a prerequisite for inferring about reliable habituation-based mechanisms of change between VRE and PCE, (i.e., respectively, the experimental and the active control arm).

Further, while comparable to superior effects of VRE over classical exposure methods on craving induction in SUDs have been reported [73, 74], to the best of our knowledge, no study has assessed the specific interest of VRCE over a non-VR cue-exposure approach in a CET context [27]. Our trial design will allow to fill the gaps in the literature by specifically assessing the effects of VR, both as a cue-reactivity exposure and cue-exposure therapy paradigm, on cocaine craving in patients with CUD. Indeed, the effects of VR as a cue-reactivity paradigm (i.e., VRE) on cocaine craving-related reactivity and exposure-dependent characteristics (i.e., sense of presence, ecological validity and cybersickness) will be contrasted to the ones of a non-VR cue-reactivity frame (i.e., pictures-based; PCE) at baseline (T0). On the other hand, the acute benefits of VRCET as a stand-alone CET will be compared to the ones a non-VR cue-exposure therapy frame (i.e., PCET) after 2 weeks of a 10-session treatment (T1). We expect to obtain superior effects of VRE or VRCET over PCE and PCET on craving induction and reduction. This may be explained by the fact that VRE environments are designed to be highly immersive (head-mounted display), interactive, multisensorial and implying 3D environments that can include diversified proximal and distal stimuli adapted to the Martinican participants ecological substance using field [21]. Hence, we hypothesize that higher self-reported sense of presence, ecological validity, and realism levels will be self-reported by participants exposed in our high-immersive VRE, as compared with in PCE. Such findings are consistent with meta-analytic evidence (*N* = 115 studies) showing the significant and medium effect of VR immersive features on sense of presence (*r* = 0.316; [75]). In addition, cue-reactivity studies in smokers and heavy drinkers suggest that sense of presence, ecological validity, and realism in VRE significantly predict [76, 77] and enhance craving induction [26]. Furthermore, there is a consensus on the fact that VRCET, compared to PCET, allows diversified exposure to motor, proprioceptive and 3D cues related with cocaine use that could not be used in vivo for safety purposes [21]. Hence, we believe that, compared to PCE, VRCE will allow for broader generalization of CET benefits (i.e., craving reduction) over the desensitization context, and prevent cue-induced craving rebound (e.g., renewal effect) in CUD [22, 23]. Finally, acceptability studies of VRCET as a stand-alone intervention or adjunct to regular treatment for SUD remain scarce [78–80]. In accordance with the findings by Arissen et al. [78], Skeva et al. [79], and Wray and Emery [80], to guarantee the acceptability of VRCE and VRCET, we focused on designing low-cybersickness VR interfaces, shortening and spacing VRCE sessions, and familiarizing therapy facilitators and patients with VRCET and VR prior to the therapeutic phase.

To conclude, a growing body of evidence suggests that enhancing cue-exposure might be of promising value for clinical addictology since craving response or reactivity to smoking cues significantly moderates craving reduction [18] and predicts drinking latency, dependence severity and withdrawal reinstatement in a CET context [19]. To do so, VR appears as a promising tool to decrease craving, notably in CUD whereby it has been understudied. Our RCT aims at filling the gaps in the literature and investigate the clinical efficacy and acceptability of VRCET over non-VR CET or CBT for CUD [27].

## Trial status

Study recruitment began in May (01st) 2023. Recruitment is estimated to be completed in May 2025 (31th). This version is the first of the protocol.

## Data Availability

This study protocol has been reported according to the Standard Protocol Items: Recommendations for Clinical Interventional Trials (SPIRIT) guidelines. Any protocol related information or material, statistical code and dataset will be made available upon request.

## Abbreviations

AWARE: Advance Warning of Relapse questionnaire
BMIS: Brief Mood Introspection Scale
CEQ – F: Craving Experience Questionnaire – Frequency subscale
CEQ – S: Craving Experience Questionnaire – Strength subscale
CSQ-8: Client Satisfaction Questionnaire – 8-item version
CBT: Cognitive Behavioral Therapy
CET: Cue-exposure therapy
CUD: Cocaine use disorder
DERS: Difficulties in Emotion Regulation Scale
DSM-IV: Diagnostic and Statistical Manual of Mental Disorders – 4th version
DTCQ-8: Drug Taking Confidence Questionnaire – 8-item version
ITC-SOPI: Independent Television Commission – Sense of Presence Inventory
MFCT: Memory-focused cognitive therapy
M.I.N.I.5.: Mini Internation Neuropsychiatric Interview – 5th version
PCE: Pictures-based cue-exposure
PCET: Pictures-based cue-exposure therapy
QCBDU: Questionnaire of Core Beliefs related to Drug Use and craving – Beliefs Related to Addiction subscale
SCID-5 CV: Structured Clinical Interview for DSM-5 ® disorders—Clinical version
SPIE: Spatial Presence for Immersive Environments questionnaire
SUD: Substance use disorder
TLFB: Timeline Followback questionnaire
URICA: University of Rhone Island Change Assessment Scale
VR: Virtual reality
VRCE: Virtual reality-based cue-exposure
VRCET: Virtual reality cue-exposure therapy
VRCET +: Virtual reality cue-exposure therapy + memory-focused cognitive therapy
VRE: Virtual reality-based exposure
3D: Three dimensional
